**Introduction**

Intravenous thrombolysis (IVT) reduces long term disability when administered early to eligible patients with acute ischemic stroke (AIS), but its benefit is strongly time-dependent.^1-4^ Moreover, earlier administration of IVT, compared with later administration, has been shown to be associated with lower risk of in-hospital mortality and hemorrhagic transformation, and better functional outcomes at discharge and at 90 days^5-7^. The AHA/ASA guidelines thus recommend to initiate tissue plasminogen activator (tPA) treatment within 60 minutes after the patient’s arrival in the emergence department.^8^ However, a cohort analysis of 1193 patients in the United States found a median DNT of 82.9 minutes.^9^ The Target: Stroke initiative was launched in 2010 to assist hospitals in providing tPA in a timely fashion. As a result, the percentage of alteplase-treated patients having door-to-needle time (DNT) of ≤60 minutes increased from 26.5% to 41.3%.^10^ In single large metropolitan comprehensive stroke centers (Helsinki and Melbourne), major reduction in DNT has been reported with multifaceted intervention.^11, 12^

[Particularly](C:/Users/Administrator/AppData/Local/youdao/dict/Application/8.9.3.0/resultui/html/index.html#/javascript:;), the delay of IVT is serious in China. Data from Chinese National Stroke Registry (CNSR) showed that the median DNT was 116 minutes, while only 17.8% of patients were treated with IVT within 60 minutes after admission.^13^ The time in CNSR was longer than those in SITS-MOST Ethos and Registry of SITS-EAST.^14, 15^ Moreover, data from the ENCHANTED indicated that Chinese patients were twice as likely as non-Chinese patients to have DNT > 60 minutes.^16^ A comprehensive program is clearly demanded in China, with ongoing monitoring of DNT as an important benchmark for quality in stroke care.

Although reducing in-hospital delay has been one of the focuses of stroke quality control in China, there is a lack of clinical trials to confirm the effectiveness of clinical interventions to reduce in-hospital delay. Improving In-hospital Stroke Service Utilisation (MISSION) study thus aimed to explore whether a multi-component behavior change intervention based on Behaviour Change Wheel (BCW) method via video teleconference could shorten DNT in China.

**Study objective**

The aim is to evaluate whether a multi-component intervention via video teleconference based on the BCW method increases the proportion of DNT ≤ 60 minutes in AIS treated with IVT.

**Design**

The MISSION is an open label, multicenter cluster-randomised clinical trial involving 22 hospitals in China. The Zhejiang Stroke Alliance developed by Zhejiang Stroke Quality Control Center (ZSQCC) has consecutively recruited stroke patients in eastern China since 2016. This trial was approved by the human ethics committee of the Second Affiliated Hospital of Zhejiang University (SAHZU), School of Medicine. The clinical trial is conducted according to the principle expressed in the Declaration of Helsinki. Written informed consent will be obtained from the participating hospital staff. Informed consent will also be obtained from patients or their legally authorized representatives for treatment with alteplase and participation in a telephone survey at 3, 6, and 12 months after the initial stroke accordance with the local hospital standards.

The clinicians in one group of hospitals will receive the PEITEM intervention, a multi-components behavior change intervention based on the behavioral principles, as described by the Behavior Change Wheel framework, whereas the clinicians in another group of hospitals as the control will only receive routine care plus stroke registry. Study activities will be divided into two periods: the Pre-intervention (January 2018 to December 2018) and the Intervention (January 2019 to December 2019). Fig A describes the study design.

**Participants: study clusters and their patients**

In China, hospitals are classified into 3 grades: community hospitals are defined as primary grade, hospitals that serve several communities are defined as secondary

grade, and central hospitals for a certain district or city are defined as tertiary grade. Only secondary or tertiary public hospitals with emergency departments (EDs) and neurological wards that admit patients with stroke and had the capacity to administer intravenous rtPA were eligible to participate in this trial. Hospitals participating in the Zhejiang Stroke Alliance meeting the inclusion and exclusion criteria are eligible for inclusion in the MISSION trial. Hospitals meeting the following criteria are eligible for the study: (1) agree to participate in the ongoing data report and continuous audit of IVT processes of care and outcomes; (2) have a stroke unit or staffing equivalent to a stroke physician and a nurse. The hospitals with fewer than 20 thrombolytic cases per year will be excluded. Only the AIS patients receiving IVT within 4.5 hours are eligible for inclusion.

**Clusters randomization and blinding**

Because the hospitals are the intervention targets, they are used as the randomization unit to minimize contamination. The hospitals will be stratifically randomized with a 1:1 allocation ratio according to their baseline proportion of IVT patients with DNT ≤60 minutes (<60%, ≥ 60% -≤ 72%, >72%) collected in the pre-intervention period. The randomization will be conducted by using a computer generated randomisation sequence, by which eleven hospitals are assigned to the intervention group and another eleven hospitals to the control group. Masking the hospital personnel and clinical investigators to site or group assignment is not possible because of the intervention nature. Nevertheless, external clinical evaluators assigned to assess the outcomes will be masked.

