**Data monitoring and quality control**

Data on all thrombolytic patients in both the PEITEM and control group will be recorded in a secure, purpose-built web-based data entry system. The system provides pre-defined logic checks to identify erroneous, illogical data entries. All patient data will be de-identified and entered by a local trained study-specific delegate who is independent from the study team at each participating hospital. The database is only accessible via a secure login system and only accessible to those approved to do so. Moreover, only the de-identified documents are preserved and monitored by an independent contract research organization throughout the study period. All recruitment will be checked by research specialists from an independent contract research organization (CRO) throughout the study period. Finally, a data quality meeting will be held quarterly to review all the hospital records and registry data.

Data will include the detailed eligibility assessment and demographics, National Institutes of Health Stroke Scale (NIHSS) score, prestroke modified Rankin Scale (mRS) score, risk factors, hemorrhagic transformation, baseline blood pressure, prior antiplatelet usage, DNT, onset-to-needle time (ONT), modified Rankin Scale (mRS) score at discharge and 90 days. mRS score at 90 days of AIS patients will be followed up with telephone questionnaires by external clinical evaluators who are blinded to the patients’ clinical data.

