**Trial management and monitoring**

The Trial Management Group (TMG) will be responsible for all aspects of local organization and the day-to-day running of the trial, including monitoring outcome data collection, and ensuring the implementation of PEITEM intervention to the participating hospitals. An independent Trial Steering Committee (TSC) will oversee the trial, and they will meet at least monthly to consider and address strategic issues. Moreover, a training physician from the department of neurology in each cluster will act as a quality coordinator. The quality coordinator’s role includes interacting with physicians once gaps in the PEITEM intervention are identified, identifying barriers for the implementation and ensuring that all the intervention are implemented. There will be a run-in period before the start of the trial. The TMG will have regular meetings with quality coordinators of the PEITEM hospitals to discuss the detail of the video conferences and to assess the infrastructures to ensure that the intervention programs can be carried out regularly after the trial begins. The evaluation of outcome will start after the run-in period. The member of a Data Monitoring Committee (DMC) will act independently of the TSC, TMG and funder, will monitor data, check the data quality submitted by the study-specific delegate, and make recommendations to the TSC on whether there are any ethical or safety reasons, if exist, why the trial should not continue. Deaths by any cause in the 1 year after hospitalization, the Serious Adverse Events (SAEs), will be recorded and reported in this trial. The DMC will monitor the occurrence of SAEs.

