**Intervention**

Hospitals assigned to the PEITEM group will implement the PEITEM intervention from January 1, 2019 through December 31, 2019. The PEITEM intervention components are grounded in the behavioral theory in the Behavior Change Wheel (BCW) method.^17^ The BCW emphasizes the importance of ensuring that proponents have the capability, opportunity and motivation to perform the desired behavior through nine interventions. The PEITEM intervention will implement six of them including **P**ersuasion, **E**nvironmental reconstruction, **I**ncentivization, **T**raining, **E**ducation and **M**odeling.

*Persuasion and Modeling* aim to foster communication between clinicians and research team to stimulate clinician’s action to shorten DNT and to provide a good example to follow. A series of measures are embedded such as setting up DNT target, time tracking with feedback, case discussion and championship experience presentation to decrease in-hospital delay. *Training and Education* can help to improve the skills and knowledge of the clinicians. The Education involve the early identification of eligible patients for IVT, rapid decision-making based on the rapid risk evaluation of hemorrhagic transformation and complication management, and the training of sustainable application of quality improvement tools; the purpose will be to help rapid diagnosis, decrease initial refusal and improve complication management. *Incentivization* encouraged stroke doctors to create expectation of reward. We will establish a pioneer award according to the number of IVT patients and the proportion of DNT ≤ 60min. Finally, we will implement the standardized medical record templates involving evidence-based performance measures to indicate *Environment reconstruction*, as a persist intervention, aiming to change the physical context of patients’ information collection. A summary of the PEITEM intervention and its link with the BCW is shown in **Fig B** and a detailed description is given in **Table A.**

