**Outcomes**

The primary outcome is the proportion of DNT ≤ 60 min in the AIS treated with IVT, indicating a fast thrombolytic treatment from hospital arrival. The secondary outcomes include the key time intervals between assessment and thrombolytic treatment (median DNT, ONT), mRS score and death at discharge, complications after IVT [symptomatic intracranial hemorrhage (sICH)] and favorable functional outcomes (score of 0 to 1 on the mRS at 90 days), which indicate the efficiency and safety of PEITEM intervention. The DNT is defined as the time between hospital arrival and the initiation of IVT. The ONT is defined as the time between the symptom onset and the initiation of IVT. sICH is defined as intracranial hemorrhage at 24 hours associated with an increase of ≥4 points of NIHSS score from baseline, according to European Cooperative Acute Stroke Study (ECASS) II trial.^18^

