Additionally, to assess whether the improvement in primary and secondary outcomes in the PEITEM group is influenced by the time window, we will conduct a sensitivity analysis with the additional inclusion of patients receiving IVT beyond 4.5 hours upon stroke onset. All patients receiving IVT beyond 4.5 hours upon stroke onset should have CT or MRI core/perfusion mismatch. For patients lost to follow-up at 90 days, we will use multiple imputation as a sensitivity analysis and compared the baseline characteristics between patients with and without mRS at 90 days. A two-tailed P < 0.05 is considered statistically significant. All analyses will be performed using SAS (version 9.4) and R software (version 4.0.5). As no detrimental problems to the participant are anticipated, there are no formal stopping rules for the trial. This trial is registered with ClinicalTrials.gov, number NCT03317639.

**Fig A** Study design and timeframe.

**
[figure not shown]
**

**Fig B** A PEITEM intervention diagram and its relationship with the BCW methods.

[figure not shown]

Abbreviations: BCW, Behaviour Change Wheel; DNT, Door-to-Needle Time.

**Table A** Description of PEITEM Intervention according to the Behavior Change Wheel Components.

| Intervention | Definition | Activity |
| --- | --- | --- |
| **P**ersuasion | Using communication to induce positive or negative feelings or stimulate action | 1. Monthly video teleconference between stroke doctors from PEITEM hospitals and research team for face-to-face problem solving; 2. Monthly DNT feedback by setting up DNT target, time tracking with feedback, discussion about the reasons of delay and improving measures through case discussion. |
| **E**nvironment Reconstruction | Changing the physical or social context | Implementation of standardized medical record templates involving evidence-based performance measures in the electronic medical record. |
| **I**ncentivization | Creating expectation of reward | Establishment of a pioneer award of IVT to the hospitals according to the number of IVT patients and the proportion of DNT ≤60min by research team. |
| **T**raining | Imparting skills | Training of sustainable application of quality improvement tools to help hospitals to establish their own personalized, efficient and stable code stroke workflow via video teleconference. |

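### The masking statement gives no described protection to the primary outcome: door-to-needle time is entered locally at unmasked hospitals, no common time source is named, and only the PEITEM arm is rewarded on the 60-minute cut

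*Protocol*

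**What the plan says.** **Outcome.** Outcomes states: "The primary outcome is the proportion of DNT ≤ 60 min in the AIS treated with IVT". It adds: "The DNT is defined as the time between hospital arrival and the initiation of IVT". Neither that section nor any other says which clock, document or person supplies the two times.

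**Masking.** Clusters randomization and blinding says of the sites: "Masking the hospital personnel and clinical investigators to site or group assignment is not possible because of the intervention nature". The next sentence is the reassurance: "Nevertheless, external clinical evaluators assigned to assess the outcomes will be masked".

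**What the evaluators do.** Data monitoring and quality control gives their task: "mRS score at 90 days of AIS patients will be followed up with telephone questionnaires by external clinical evaluators". The same section lists DNT among the data collected and has patient data entered by a trained local delegate at each hospital. That delegate is independent of the study team; nothing is said about masking.

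**What differs by arm.** Table A describes incentivization as "Establishment of a pioneer award of IVT to the hospitals according to the number of IVT patients and the proportion of DNT ≤60min by research". It also lists monthly DNT feedback with a target and time tracking. For the record system, Intervention says: "we will implement the standardized medical record templates involving evidence-based performance measures". Under Design, control hospitals have routine care and the registry only.

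**Checks applying to both arms.**
- Participants makes ongoing data reporting and continuous audit of thrombolysis care a condition of hospital entry.
- Data monitoring and quality control provides logic checks in the entry system, CRO monitoring of de-identified documents, CRO checks of recruitment, and a quarterly review of hospital records and registry data.
- Trial management and monitoring has a data monitoring committee (DMC) check the quality of the delegates' data. It also gives the Trial Management Group several duties, "including monitoring outcome data collection, and ensuring the implementation of PEITEM intervention to the participating hospitals".

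**The concern.** A reader of the blinding section would take the masked evaluators to cover the trial's outcomes, the primary one included. They are not described as doing so. An open-label design is unavoidable here and is not the defect. The defect is that the one safeguard offered against it does not reach the endpoint on which the trial will be judged.

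This matters more than in most open-label trials because the intervention touches the conditions under which the endpoint is recorded. In one arm only, the hospital's recorded proportion at or below 60 minutes counts towards an award, is fed back monthly against a target, and is produced alongside a new record template. If these lead to shorter recorded times without shorter real times, the error favours PEITEM at a fixed cut. Stratifying on the baseline proportion does not protect against this, because the incentive begins after randomization.

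**Working it through.** **1. Does any described procedure protect the two times?**

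| Safeguard | Covers DNT? | Described as masked? | Described as checking arrival and needle time against an independent source? |
|---|---|---|---|
| External evaluators | Not described; 90-day mRS only | Yes | No |
| Local delegate | Yes, enters data | No | No |
| Logic checks | Yes, on entered values | Not applicable | No |
| CRO document monitoring | Plausibly | No | No |
| Quarterly review of records and registry | Plausibly | No | No |
| Audit condition for hospitals | Plausibly | No | No |
| DMC data-quality check | Plausibly | No | No |

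No row combines coverage of DNT with masking or with an independent time source.

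**2. Precision of the primary comparison.** Sample size gives 1424 patients, 22 hospitals, ICC 0.05 and a 62% surveyed baseline; allocation is 11 hospitals per arm.

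- Cluster size: 1424/22 = 64.7
- Design effect: 1 + (64.7 − 1) × 0.05 = 4.19
- Effective number per arm: 712/4.19 = 170
- Power for 55% against 70% at this effective number: 81.8%, in line with the stated 80%, so the approach fits the plan's own inputs.
- Standard error at 62% against 65%: √[(0.62 × 0.38 + 0.65 × 0.35)/170] = 0.052

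**3. How far could a small recording shift move the proportion?** The documents give neither the spread of DNT nor any recording error. Assume log-normal DNT with 62% at or below 60 minutes, log-SD 0.35 to 0.55, no true effect, and every PEITEM time recorded d minutes shorter. The recorded proportion is then Φ[0.305 + ln((60 + d)/60)/SD], where Φ(0.305) = 0.62.

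| Log-SD | Gain at d = 2 | Gain at d = 5 |
|---|---|---|
| 0.35 | 3.5 points | 8.3 points |
| 0.45 | 2.7 points | 6.6 points |
| 0.55 | 2.2 points | 5.4 points |

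**4. Effect on the false-positive risk.** Two-sided 5% test, normal approximation:

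- Spurious 3 points: 0.03/0.052 = 0.57 standard errors, P(|Z| > 1.96) = 8.9%
- Spurious 5 points: 0.05/0.052 = 0.96 standard errors, P(|Z| > 1.96) = 16.2%

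**5. A second illustration, by misclassification.** Suppose a share r of PEITEM patients with true DNT above 60 minutes is recorded as at or below 60. At a true rate of 62% the spurious gain is r × 38 points:

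- r = 10%: 3.8 points, about an 11% chance of significance
- r = 20%: 7.6 points, about 31%
- To mimic the full 15-point target: r = 15/38 = 39%

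A slight shift does little; only substantial misrecording would imitate the planned effect.

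**The case against.** The strongest reply is that the protocol has more data oversight than the blinding section suggests: CRO document monitoring, a quarterly review that includes hospital records, an audit condition on every hospital, and a DMC that checks submitted data. None is confined to one arm. This stands, and it lowers the risk. It does not remove it, because none is described as masked or as tied to an independent source for the two times. A plausible time a few minutes off could pass all of them.

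Second, DNT is also analysed as a continuous outcome, and a benefit produced only by shaving times at the cut would barely move the mean. For example, if 10% of late cases, 3.8% of patients, were each recorded 3 minutes shorter (an assumed figure), the mean would fall by 0.038 × 3 = 0.11 minutes. This stands against threshold shaving. It does not help against a general shift, which moves both analyses together.

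A reader might infer several stronger points that the documents do not support:
- *That unmasked clinicians write the times and the delegate can only copy them.* This is likely, but the protocol names no recorder.
- *That monthly case review corrects wrong long times and leaves wrong short ones.* Table A describes discussion of delays and improvements, not amendment of data.
- *That the template alters door or needle times.* It is said only to carry performance measures, and could equally improve accuracy.
- *That the CRO looks at recruitment only.* It also monitors documents.
- *That the people delivering PEITEM oversee outcome data.* A quality care initiative team implements PEITEM; the Trial Management Group ensures implementation and monitors data collection. The protocol does not say they are the same people.

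**Conclusion.** The point holds as a gap in ascertainment, not as evidence of bias. The masking sentence is broader than anything the protocol describes and gives the primary outcome no described protection. DNT is entered locally at unmasked hospitals without a named common source, while one arm alone is rewarded and reviewed on the same 60-minute measure.

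The size of any bias cannot be obtained from the documents. The figures of about 2 to 3.5 points for a 2-minute shift, and a false-positive risk of about 9% at 3 spurious points or 16% at 5, rest on an assumed log-normal shape, an assumed spread, an assumed uniform shift and a normal approximation at the planned size and ICC. It would go too far to say that a positive result could not be told apart from favourable time-keeping. The existing checks and the continuous analysis offer partial protection, so this is a should-fix rather than a must-fix.

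**What to change.** 1. In Clusters randomization and blinding, limit the masking statement to the 90-day mRS, and say plainly that DNT is not assessed by masked evaluators.
2. Name the same source for door time and for needle time in both arms, outside the PEITEM record template. Prefer system time stamps, with a named fallback where a hospital has none.
3. Lock each month's arrival and needle times before the PEITEM feedback conference, so that discussing cases cannot alter data in one arm only.
4. Direct the existing CRO monitoring to check these two fields against source in both arms, at least for recorded DNT near 60 minutes.

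The cost is protocol, data-manual and monitoring-plan wording, a monthly lock, and some redirected CRO effort. No extra patients or procedures are needed. One limit remains: where no electronic stamp exists, needle time may still rest on a record kept by hospital staff, so the change reduces the exposure without abolishing it.
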